## Introduction

 The target trial emulation (TTE) framework has been proposed to identify and avoid potential biases when estimating the causal effects of treatment using observational data. The strategy entails specifying protocol components of a real or hypothetical randomised controlled trial (RCT) (the ‘target trial’), including the causal estimand of interest, and detailing the emulation of this using the available observational data. The framework has the potential to minimise common time-related biases in pharmacoepidemiology and provides an opportunity to validly address a breadth of research questions, including about comparative effectiveness and treatment discontinuation.^1^,^4^

TTE has been adopted in many therapeutic areas, including cystic fibrosis (CF).^5^,^7^ CF is a life-shortening condition, caused by mutations in the CF transmembrane conductance regulator (CFTR) gene, which affects multiple organ systems, including the lungs, liver, digestive tract and reproductive organs. There are over 11 000 people in the UK living with CF.^8 9^ People with CF often face substantial treatment burden, requiring complicated and time-consuming treatment plans daily to maintain their health.^10^ This includes multiple different daily oral and inhaled therapies on a long-term basis as an integral component of management for the majority of people with CF.

Inhaled corticosteroids (ICS) are commonly used by people with CF, with the purported aim of targeting inflammation and/or symptoms of wheeze. However, the current evidence for risks and benefits of ICS in CF is uncertain, with known adverse effects on growth and adrenal function.^11^ A Cochrane review of ICS effectiveness in people with CF concluded that none of the currently published trials could conclude effectiveness at reducing lung inflammation; despite this, ICS are still widely prescribed.^9^ The only trial included which was found to have a low risk of bias was the CF-WISE (Withdrawal of Inhaled Steroids Evaluation) trial (PMID:16556691).^11 12^ CF-WISE investigated the effect of discontinuing ICS on risk of pulmonary exacerbation in the UK and concluded that it was safe for most patients to discontinue.^12^

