## Methods and analysis

### Data source

The UK CF Registry (UKCFR) is a centralised national database sponsored and managed by the CF Trust, which collects real-world data from all specialist CF centres in the UK.^15^ It holds data on an estimated 99% of the UK CF population covering demographic and longitudinal clinical data and was highlighted by the UK National Institute for Health and Care Excellence real-world evidence framework as an exemplar data source for evidence generation.^16^

Data collection for the UKCFR began in 1996 and is primarily structured around annual review visits, taking place approximately 1 year apart. In addition, demographic data including sex, ethnicity, diagnosis data and genotype are collected at enrolment into the Registry and usually remain time-invariant. Information is captured annually on events or conditions that have happened since the previous annual review, including complications, infections, treatments and hospital admissions. Other information collected at the date of each annual review includes results from pulmonary function tests, weight and height. Extracts of data recorded at annual reviews are provided to researchers for approved projects. In 2016 variable domains were added, including exact start and stop dates of medications.

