#### Prevalent new-user design

In the PNUD, to be included in the base cohort individuals should have a diagnosis of CF, be aged ≥6 years, have a forced expiratory volume in 1 s (FEV _1_)≥40% predicted at most recent annual review, and prescribed ICS for >3 months before the date of ICS discontinuation, for both the discontinuer in each exposure set and their corresponding continuers. Excluded are those who were prescribed oral corticosteroids and/or intravenous antibiotics in the 1 month prior to the ICS discontinuation date, for both the discontinuer in each exposure set and their corresponding continuers. Exclusion of individuals taking higher doses of ICS as specified in the target trial is not possible in the emulated trial as dosage information is unavailable in the UKCFR.

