#### Covariates

In the emulated trials, treatment discontinuation or continuation is not randomised and so measured potential confounders of the relationship between ICS discontinuation and clinical outcomes must be adjusted for to meet the assumption of no unmeasured confounding, a requirement for unbiased causal effect estimation.^30^

Based on a priori clinical expertise, we will adjust for the following covariates at baseline: age, sex, genotype, body mass index z-score, CF-related diabetes, FEV_1_% predicted, home and hospital intravenous antibiotics, hospital admissions, *P. aeruginosa* infection, *Burkholderia* infection, non-tuberculous mycobacteria infection, allergic bronchopulmonary aspergillosis, pancreatic insufficiency, liver disease, inhaled bronchodilator use (captured as a separate variable to ICS), asthmatic status (as a proxy to atopic status specified in CF-WISE), inhaled antibiotic use and mucoactive therapy use (hypertonic saline, mannitol and DNase).

For both the PNUD and sequential trials design, these covariates will be recorded at the nearest annual review date preceding time zero. Since ICS stopping dates may occur at any point between successive annual reviews, stopping dates will occur at various time intervals following baseline annual review across individuals. Therefore, time from previous annual review (in months) to time zero for both the discontinuers and continuers will be adjusted for in the analyses.

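### Oral corticosteroid use before the one-month exclusion window is left out of the fixed adjustment list without a stated reason, although earlier intravenous antibiotic use is adjusted for

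*Protocol article*

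**What the plan says.** The Covariates section of the protocol article sets its own standard: "measured potential confounders of the relationship between ICS discontinuation and clinical outcomes must be adjusted for". It then gives the list, introduced by "we will adjust for the following covariates at baseline: age, sex, genotype, body mass index z-score". The list has 18 named items, including home and hospital intravenous antibiotics, hospital admissions, FEV1% predicted, allergic bronchopulmonary aspergillosis, inhaled bronchodilator use and asthmatic status. Time since the previous annual review is added. The wording is closed, with nothing to mark the items as examples, and oral corticosteroids do not appear.

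Oral corticosteroids enter the plan only through eligibility. Under Inclusion and exclusion criteria, for the prevalent new-user design (PNUD): "Excluded are those who were prescribed oral corticosteroids and/or intravenous antibiotics in the 1 month prior to the ICS discontinuation date". The sequential trials design applies the same criteria at each trial's time zero.

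The list carries the whole adjustment. Table 1 takes assignment to be random given ICS history and these covariates. Main analysis uses them in the PNUD propensity score and in the per-protocol censoring weights. The sequential design adjusts for the baseline confounders and derives its censoring weights as in the PNUD, separately within each trial.

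**The concern.** A course of oral corticosteroids some months before time zero plausibly marks reactive or inflammatory airway disease. That could bear both on whether a clinician stops an inhaled steroid and on the risk of a later exacerbation treated with intravenous antibiotics. Under the plan, two people who match on the listed covariates are treated as exchangeable even if one had such a course two or more months ago and the other had none.

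If this matters, the primary hazard ratio and the risk difference are affected in both designs, because both rely on the same list. Agreement between the two designs would then give no reassurance on this point.

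**Working it through.** **How the plan handles two exposures named in one exclusion sentence**

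| | Last month before index date | Earlier use |
|---|---|---|
| Intravenous antibiotics | Excluded | Adjusted for (Covariates) |
| Oral corticosteroids | Excluded | Neither excluded nor adjusted for |

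No reason is given for the difference.

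**Is the variable held?** The exclusion rule can be applied only if oral corticosteroid prescriptions are available, so availability is an inference. Data source says that treatments since the previous review are captured annually, which would supply a review-level indicator. Two cautions apply. The feasibility section reports checks on ICS dates and intravenous episodes only. The eligibility footnote in the Figure 4 caption names intravenous antibiotics but not oral corticosteroids, and should be reconciled with the text.

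**What look-back is possible?** Exact medication dates were added in 2016 and eligibility opens on 1 January 2016. A dated 12-month look-back is therefore not assured for time zeros during 2016, which is 12 of the 30 months. An indicator taken at the baseline annual review avoids this and is timed like the other covariates. It misses courses given after that review and before the exclusion month.

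**Possible size.** The plan states no figure to reproduce, and it gives no prevalence of earlier oral corticosteroid use and no association with outcome. All inputs here are assumptions. For a binary omitted confounder,

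bias factor = [1 + p1(RR − 1)] / [1 + p0(RR − 1)],

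where p1 and p0 are the prevalences in discontinuers and continuers left unbalanced after the listed covariates, and RR is the effect on exacerbation.

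| Assumed RR | 10% vs 5% | 40% vs 20% |
|---|---|---|
| 1.0 | 1.00 | 1.00 |
| 1.2 | 1.02/1.01 = 1.01 | 1.08/1.04 = 1.04 |
| 1.5 | 1.05/1.025 = 1.02 | 1.20/1.10 = 1.09 |
| 2.0 | 1.10/1.05 = 1.05 | 1.40/1.20 = 1.17 |

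If use is less common in discontinuers, the factors invert, down to 1/1.167 = 0.86.

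The sign depends entirely on which group has more earlier use:

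- 8% vs 15% with RR 1.5 gives 1.04/1.075 = 0.97; swapping the groups gives 1.03.
- 5% vs 20% with RR 2.0 gives 1.05/1.20 = 0.88 (0.875 before rounding); swapping gives 1.14.

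Either direction can be argued. Steroid burden as a motive for stopping implies more earlier use in discontinuers. Reactive airway disease as a motive for continuing implies less.

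**Scale for comparison.** CF-WISE reported a hazard ratio of 1.07 (0.68 to 1.70), so SE(log HR) = [ln 1.70 − ln 0.68]/(2 × 1.96) = 0.916/3.92 = 0.234. The estimate lies ln 1.07 = 0.068 from the null, whichever arm is the reference. Of the two cases above, the first moves the log hazard ratio by 0.033 and the second by 0.134. Both are small beside 0.234. Only the second exceeds 0.068, the shift needed to change the direction of an estimate that close to 1. Direction is part of the first benchmarking criterion.

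**The case against.** The strongest reply is that much of what earlier oral corticosteroid use would carry is already in the list: asthma, allergic bronchopulmonary aspergillosis, bronchodilator use, FEV1%, intravenous antibiotics and admissions. The most recent users are excluded, the list rests on clinical judgement, and residual confounding is acknowledged. A variable that drives stopping but not the outcome causes no confounding, and adjusting for it only adds variance. Most of this stands as a limit on size. It does not explain the omission. The proxies are mainly diagnoses and maintenance treatments and do not record recent steroid-requiring episodes. Quantitative bias analysis is aimed at unmeasured confounding, and Sensitivity analyses says only that it will be considered.

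A reader might go further and say that height should be adjusted for too. It is available ("Other information collected at the date of each annual review includes results from pulmonary function tests, weight and height"), the Introduction cites "known adverse effects on growth and adrenal function", children from age 6 are eligible, and a short child can have a normal BMI z-score. The documents do not support this. They list growth as a harm of ICS but do not say it is why people stop. Nothing links stature to exacerbation within 6 months once age, sex, BMI z-score, FEV1%, pancreatic insufficiency and the rest are adjusted for.

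A reader might also infer that avoidable bias has been shown, or take one of the factors above as its size. Neither follows, since every input is assumed and the sign is open.

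**Conclusion.** The point holds for oral corticosteroids only. By the plan's own standard, earlier oral corticosteroid use is a potential confounder that appears to be recorded, and it is left out of a fixed list without a reason, while the parallel variable for intravenous antibiotics is included. It deserves correction before analysis because one list serves both designs and all the weights.

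The size of any residual bias is unknown. Under the assumed ranges it runs from none to a factor of about 1.17, or 0.86 in the other direction, before allowing for how far the listed proxies narrow the imbalance. The conclusion rests on two assumptions: that the registry field exists beyond the exclusion month, and that earlier use bears on the outcome after the listed covariates. The second is plausible but is not stated in the document.

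**What to change.** Add to the Covariates list an indicator of any oral corticosteroid use since the previous annual review, taken at the baseline annual review like the other covariates. Use it in the PNUD propensity model, the sequential outcome models and the censoring-weight models of both designs. Confirm first that the field is held and complete. If it is not, say so in Limitations and name earlier oral corticosteroid use as a target of the bias analysis. Where exact dates allow, a dated look-back could serve as a sensitivity analysis. Height z-score should stay out of the main models and at most be examined in a sensitivity analysis.

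The cost is one model term and slightly more variable odds weights, with at most 536 discontinuers before the other exclusions. It is felt most in the sequential censoring models, which are fitted within each trial: with monthly trials, 536/30 is about 18 discontinuers per trial on average.

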### Data analysis

#### Causal estimands

Causal estimands are a way to clearly describe the target of treatment effect estimation.^31^ In an RCT, the average treatment effect in the treated (ATT) and an alternative estimand, the average treatment effect in the whole population (ATE), are the same due to randomised treatment assignment.^24^ In observational data, however, the ATT and the ATE differ because the characteristics of the treated subgroup differ from those of the whole eligible population. In our study, the ATT targets the question: ‘how would the outcomes in those discontinuing ICS have differed, on average, had they continued on ICS?’. By contrast, under the ATE, we ask the question: ‘how would the outcomes in the population differ, on average, had everyone discontinued ICS versus continued on ICS?’.^24^

The PNUD specifically targets an ATT, whereas the sequential trials design, which makes use of all continuers in the study (figure 4) can be used to estimate an ATE or ATT through different analysis steps. This work will establish which estimands are targeted in both study designs, interpret any differences between them and explore how data obtained under the sequential trials design can be used to target the ATT as well as an ATE, and hence allow valid comparison between results obtained under the two designs.

HRs for time to pulmonary exacerbation associated with ICS discontinuation will be the primary causal estimand of interest. HRs are assumed to be constant over time and will allow for empirical benchmarking of the findings to the CF-WISE trial. The marginal risk difference will also be estimated to compare the risk of pulmonary exacerbation associated with discontinuation up to a time horizon of 6 months following treatment assignment.

#### Main analysis

##### Prevalent new-user design

In the PNUD, continuers within each exposure set will be weighted to resemble the discontinuers using propensity score (PS) weighting methods described elsewhere as time-stratified standardised morbidity ratio weighting.^32^,^34^ We will fit a logistic regression model across all exposure sets with treatment discontinuation as the outcome, adjusting for time and the covariates specified in *Covariates*, to estimate the probability of discontinuing versus continuing ICS, deriving weights as follows: discontinuers will receive a weight of 1, and continuers will be weighted by their odds of discontinuing (ie, where PS denotes an individual’s probability of being a discontinuer conditional on their covariate set, and continuers are weighted as PS/(1−PS)).^35^

A weighted Cox proportional hazards model, including treatment status (discontinue versus continue) as the only covariate, will be used to estimate HRs for time to first pulmonary exacerbation, along with bootstrapping used to obtain corresponding 95% CIs. Individuals are censored at the time of death or transplant in this analysis. Marginal cumulative incidence curves will also be estimated under the two treatment strategies. This will be achieved by applying a weighted Aalen-Johansen estimator separately in the discontinuers and the continuers. The analysis takes account of the competing events of death or lung transplant.^36^

The above approach gives an estimate of the ITT effect. Estimation of the PP effect will involve censoring individuals who deviate from their baseline treatment status, which will be accounted for using inverse probability of censoring weighting (IPCW). The probability of remaining uncensored up to a given time will be estimated based on a Cox regression where censoring is the outcome and adjustment is made for the baseline covariates (the same covariates adjusted for in the PS-based weighting procedure). These probabilities will be used to derive IPCW weights to be used in the analysis (weighted Cox proportional hazards model and weighted Aalen-Johansen estimator).^37^

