Outcomes	Primary: time to first pulmonary exacerbation Secondary: (i) lung function change (FEV_1_ and FVC), (ii) new/unplanned courses of intravenous antibiotics and (iii) rescue bronchodilator usage	Same as CF-WISE	Primary: same as target trial, with different definition for pulmonary exacerbation; defined as a course of hospital or home intravenous antibiotics (see *Outcomes*). Secondary: (i) mean change in FEV_1_% predicted and FVC% predicted. Secondary outcomes (ii) and (iii) will not be assessed due to similarity of UKCFR definitions for intravenous antibiotic courses and pulmonary exacerbation and inability to define rescue bronchodilator use, respectively.
Causal contrasts	Intention-to-treat	Same as CF-WISE	Observational analogue of intention-to-treat and per-protocol
Statistical analysis	For primary outcome, a Cox proportional hazard regression was used. The Wilcoxon rank sum test was used to compare % change in lung function. ORs or relative risks were estimated to compare categorical outcomes (ii and iii). Prespecified subgroup analyses for age, atopic status, dose of ICS, baseline FEV_1_ and *Pseudomonas aeruginosa* infection status.	Same as CF-WISE	Prevalent new-user design: Weighted Cox proportional hazards regression will be used to estimate HRs and 95% CIs. Marginal survival curves and risk difference at 6 months will be estimated. Sequential trials design: Adjusted Cox proportional hazards regression to estimate HRs and 95% CIs. Marginal survival curves and risk difference at 6 months estimated using standardisation. For both designs, intention to treat and per-protocol estimates will be calculated, the latter using inverse probability of censoring weights to account for informative censoring where individuals switch from assigned treatment during follow-up. For information on analysis for secondary outcomes (lung function) see online supplemental material appendix 1 .

* When the target trial is based on an existing RCT this corresponding RCT is termed the reference or index trial. Some aspects of the index trial and target trial may differ because it is not possible to emulate them in observational data, and separating the index and target trials can help to highlight where any differences in findings from the emulated trial compared with the index trial may arise.^48 49^

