#### Treatment strategies

The treatment strategies for the TTEs differ from the target trial due to lack of a placebo control. Instead, these analyses consider ICS discontinuation based on prescription data as the ‘treatment’ of interest and continued ICS use as the comparator treatment strategy. Whereas the index trial investigates discontinuation of fluticasone propionate only, the target trial and emulated trials are more pragmatic and will include all types of ICS (including in combination with bronchodilators). This reflects the heterogeneity of specific ICS or IC combination treatments documented within the UKCFR.

Discontinuation will be conceptualised as a point treatment strategy (ie, non-time-varying), where treatment status is determined at a single time point (time zero) for both ICS discontinuers and continuers.

These analyses will first estimate the observational analogue of an intention-to-treat (ITT) effect, which is the effect of being assigned to a treatment status.^24^ We will also target a per-protocol (PP) effect, which is the effect of adhering to the assigned treatment strategies. If in the real world individuals deviate from their assigned treatment (ie, discontinuers switch back to being on ICS and vice versa), the ITT and PP estimands differ and the ITT may be less relevant. See *Main analysis* for details.

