##### Sequential trials design

In the sequential trials design, the sequence of emulated ‘trials’ will be constructed and then pooled (ie, stacked) together for the analysis. Adjusted Cox proportional hazards regression models will be used to estimate conditional HRs, including treatment status at the start of each trial and adjusting for the baseline confounders in each trial.

Conditional HRs (adjusted for baseline covariates) from a cause-specific model for pulmonary exacerbation will be presented. We will also obtain estimates of marginal cumulative incidences based on the cause-specific hazard models for pulmonary exacerbation, and for the competing events of death and transplant, followed by empirical standardisation. Marginal risk differences at 6 months will be obtained from the marginal cumulative incidences. Bootstrapping will be used when estimating all 95% CIs.^38^

As in the PNUD, in addition to the ITT estimate, the PP effect will be estimated by censoring individuals when they deviate from their assigned treatment strategy within each artificial trial. IPCW weights will be derived as specified in the PNUD above, but separately in each artificial trial.

See online supplemental material appendix 1 for additional information on estimands, data analysis and analysis of secondary outcomes.

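### The per-protocol censoring weights use only covariates from before time zero, so they correct informative switching only under an assumption the plan does not state

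*Protocol article*

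**What the plan says.** All references are to the protocol article.

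- **What is censored** (Main analysis, Prevalent new-user design): "Estimation of the PP effect will involve censoring individuals who deviate from their baseline treatment status". This applies to both arms; Treatment strategies foresees that "discontinuers switch back to being on ICS and vice versa".
- **What the weights condition on** (same section): "adjustment is made for the baseline covariates (the same covariates adjusted for in the PS-based weighting procedure".
- **When those covariates are measured** (Covariates): "these covariates will be recorded at the nearest annual review date preceding time zero".
- **The sequential design** (Main analysis, Sequential trials design): "IPCW weights will be derived as specified in the PNUD above, but separately in each artificial trial".
- **What the weights are for** (Table 1, Statistical analysis row): "using inverse probability of censoring weights to account for informative censoring where individuals switch from assigned treatment during follow-up".

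Table 1 defines both strategies as sustained for the whole of follow-up. Follow-up for the primary outcome ends at the first course of intravenous antibiotics, death, transplant or 6 months. Quantitative bias analysis is only to be considered, and it addresses unmeasured confounding; informative switching is not named.

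**The concern.** The primary event is an intravenous course, so milder worsening can come before it. That worsening happens after time zero and may prompt someone to restart ICS, or in the other arm to stop. The person is then censored before any event. The people who stand in for them share their arm and baseline covariates but are, on average, less likely to have worsened. Covariates from before time zero cannot tell the two groups apart.

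At stake is the per-protocol effect, the plan's estimate of stopping and staying off. Treatment strategies says that the ITT effect may be less relevant if people deviate, so readers would lean on the per-protocol result in just the setting where its weights are most exposed.

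**Working it through.** The plan gives no crossover rate, event count or per-protocol effect, so there is no figure of its own to reproduce. The check asks whether the weights can do what Table 1 says, and in which direction they fail.

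**1. What the weights can and cannot change.** Under the plan the weight at time t is 1/K(t | x), where K is the modelled probability of remaining uncensored and x the baseline covariates. Suppose, generously, that K is also fitted by arm. Everyone with the same arm and x still has the same weight at t, whether or not they have worsened. Write h for the event hazard when well, m for its multiplier after worsening, and π for the share of the risk set that has worsened. The hazard in that stratum is h × [1 + (m − 1)π], and a weight common to the stratum leaves π as censoring has made it.

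**2. How censoring moves π.** Assume background switching of 1% per week and switching after worsening of s per week. Each week the odds of being worsened among those still uncensored are multiplied by (1 − s)/(1 − 0.01):

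- s = 1%: 0.99/0.99 = 1.000, no distortion
- s = 5%: 0.95/0.99 = 0.960
- s = 10%: 0.90/0.99 = 0.909
- s = 25%: 0.75/0.99 = 0.758

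**3. Effect on the estimate.** An expected-value model was run in weekly steps for 26 weeks, solving the Cox score on the expected risk sets. All rates are assumptions: event hazard 0.8% or 1.6% per week in two baseline strata, m = 5, and worsening at 5% per week in discontinuers against 2% in continuers. With no crossover the HR is 1.45 and the 6-month risk difference +12.4 points. Baseline-only weighting gives:

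| Who switches more after worsening | HR | Risk difference (points) |
|---|---|---|
| Nobody (1% throughout) | 1.45 | +12.4 |
| Discontinuers, 5% per week | 1.32 | +8.9 |
| Discontinuers, 10% per week | 1.17 | +4.9 |
| Discontinuers, 25% per week | 0.91 | −3.1 |
| Both arms, 10% per week | 1.38 | +9.8 |
| Continuers only, 10% per week | 1.70 | +17.3 |

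Under a true null (worsening at 2% per week in both arms, m = 5), switching at 10% per week gives HR 0.85 if only discontinuers respond to worsening, 1.00 if both arms do, and 1.17 if only continuers do.

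**4. A milder set of assumptions.** Take a 6-month risk of 41% in continuers, worsening at 6% per month and 1.8 times faster off ICS, a tripled hazard after worsening, and base restarting of 3% per month. The true HR is 1.135. If worsening multiplies restarting by 3, 5 or 10, baseline-only weighting gives 1.11, 1.09 or 1.05. On these rounded figures, between 0.025/0.135 = 19% and 0.085/0.135 = 63% of the excess is lost.

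**5. Does conditioning on the worsening help?** In a simulation of the step 4 setting, weights that used the time-updated marker returned 1.13 to 1.14. The remedy works when the driver of switching is observed.

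**The case against.** Four objections have force.

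*Direction.* Deviators are censored in both arms, and no passage gives crossover rates or reasons. A reader might infer that the per-protocol estimate will drift towards stopping being safe. The documents do not support that: the table shows no bias, mild attenuation or a reversed bias, depending on who switches and why. That restarts usually follow worsening is plausible, but it is an assumption.

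*Benchmarking.* A reader might also infer that the flaw would manufacture agreement with CF-WISE. The CF-WISE contrast is intention-to-treat, its observational analogue is estimated first and is untouched, and Benchmarking does not single out the per-protocol estimate.

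*Data.* It is tempting to say that the registry can show the worsening. Data source does say "In 2016 variable domains were added, including exact start and stop dates of medications", but does not list which medicines. The feasibility section specifically describes only ICS and intravenous antibiotic dates, and the latter mark the outcome. Clinical measures are mainly annual while follow-up is 6 months. A bronchodilator start after stopping ICS may simply replace a combination product.

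*Size.* The larger shifts need heavy crossover: 35%, 47% and 61% of discontinuers are censored in the three restart rows of the table. In the milder setting, 41% of at most 536 discontinuers is about 220 events, so SE(log HR) is at least 1/√220 = 0.067. The log-HR shifts are ln(1.135/1.11) = 0.022, ln(1.135/1.09) = 0.040 and ln(1.135/1.05) = 0.078; only the last exceeds one SE.

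These points limit direction, reach and size. They do not rescue the censoring model: the main text fixes it on baseline covariates. Appendix 1 is not shown and might add detail, but nothing in the text shown brings in post-baseline predictors or states the independence assumption.

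**Conclusion.** The point holds for the per-protocol estimand in both designs. The planned weights deliver what Table 1 says only if switching is independent of post-baseline health given baseline. If it is not, the per-protocol hazard ratio and risk difference are biased, towards no harm where deterioration-driven restarting in discontinuers dominates and away from it where stopping in continuers dominates. If both arms respond alike, the bias is smaller, and it vanishes under a true null.

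The amount cannot be derived from the documents. The figures above show only that it could range from negligible to enough to change the sign of the effect under assumed rates. The ITT analogue, and its comparison with CF-WISE, stand. This should be changed before analysis, but it does not undermine the study as a whole.

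**What to change.** In both designs, replace the baseline-only censoring model with a time-updated one fitted by arm:

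- Split follow-up into short intervals. Add lagged predictors from after time zero wherever the registry dates them, such as starts or stops of other medicines, and FEV1% predicted and infection status from any annual review inside follow-up.
- Check first which medicines have usable dates. Do not read a bronchodilator start as worsening when it may replace a combination product.
- Use stabilised, truncated weights, and report the baseline-only version alongside as a comparison.
- Where no such predictor exists, state the independence assumption, report switching by arm and timing, and add a sensitivity analysis for informative switching.

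The cost is analysis-plan wording, a check of date quality, and programming on registry data. Weights will be somewhat more variable and per-protocol intervals wider. With mainly annual clinical measures the correction may be only partial, which is why the reporting and sensitivity analysis matter.
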